#### Peripheral vascular function

Measurements of the reactive hyperemic index (RHI) and the augmentation index, respectively, will be measured with peripheral arterial tonometry (PAT) under standardized conditions in a quiet dark room. A pneumatic probe will be placed on the tip of each index finger and connected to a plethysmographic device (EndoPat-2000, Itamar Medical Ltd, Caesarea, Israel). After this PAT measurements will be made before and during reactive hyperemia as previously described [31] in order to derive RHI, a measure of microvascular endothelial function, and the augmentation index, a measure of arterial stiffness, normalized to a heart rate of 75 bpm, respectively.

#### Oral glucose tolerance test (OGTT)

The participants will be asked to drink 0.5 L of a 15% glucose solution within a 5-min period. Blood samples will be collected prior to the 75 g glucose intake as well as after 15, 30, 60, and 120 min to measure plasma glucose and insulin. Glucose tolerance will be measured by the 2 hour value and the area under the curve for glucose. To determine whole body insulin sensitivity the insulin sensitivity index (ISI) proposed by Matsuda and Defronzo will be calculated from fasting and mean plasma glucose and insulin concentrations obtained from the measuring time points during the OGTT [32].

#### Blood pressure

After a 1½ hr resting period during the OGTT, blood pressure will be measured with a digital sphygmomanometer (OMRON-M7) 5 times on the left arm at 2 min intervals. The average of the 5 measurements will be recorded for subsequent analysis.

#### Blood sampling and analyses

Blood samples will be obtained from a cubital vein and serve as a screening tool at baseline. Thus, hemoglobin and iron status will be measured to avoid inclusion of patients with anemia (Sysmex XE-2100, Sysmex America, Inc., Lincolnshire, IL, USA). Coagulation markers of International Normalized Ratio, activated partial thromboplastin time (APTT) and trombocytes will be measured to rule out coagulopathy (ILS ACL TOP, Instrumentation Laboratory, 1930 Zaventem, Belgium and Sysmex XE-2100, Sysmex America, Inc., Lincolnshire, IL, USA). Serum concentrations of creatinine will be measured to rule out kidney disorders and levels of aminotransferases, alkaline phosphatase and bilirubine to rule out liver disorders (MODULAR analyzers, Roche Diagnostics, Mannheim, Germany). In addition all blood samples will be analyzed at baseline, 12 and 32 weeks for total cholesterol, low-density lipoprotein cholesterol, high-density lipoprotein cholesterol, triglycerides, and glycosylated hemoglobin, respectively, by automated analyzers (Cobas Fara, Roche, Neuilly sur Seine, France) using enzymatic kits (Roche Diagnostics, Mannheim, Germany, and Tosoh G7, Tosoh Europe, Tessenderlo, Belgium). All of the above mentioned blood markers will be analyzed in the Department of Clinical Biochemistry at Copenhagen University Hospital Rigshospitalet, Denmark.

All samples will also be analyzed for bone markers, including procollagen type I C propeptide, osteocalcin, C-terminal telopeptide, tartrate-resistant acid phosphatase 5b and leptin, using ELISA and AlphaLISA apparatus (PerkinElmer, Cambridge, United Kingdom) at the Scientific Laboratory at the University of Exeter, United Kingdom.

### Patient-reported outcomes

Information on socio-demographic and lifestyle characteristics will be collected at baseline [33]. Health-related quality of life outcomes will be measured using the eight sub scales of the Medical Outcomes Study Short Form [34] and the 15 subscales of the European Organization for Research and Treatment of Cancer (EORTC QLQ-C30) [35]. Diagnosis-specific symptoms and side-effects will be measured with the supplement EORTC QLQ-PR25. Anxiety and Depression will be measured with the two subscales of the Hospital Anxiety and Depression Scale [36,37]. Social support and network will be measured with The Multidimensional Scale of Perceived Social Support [38]. Leisure time physical activity level will be examined using a self-administrated questionnaire classifying patients in the following groups: I) sedentary; II) walking or cycling for pleasure; III) regular physical exercise at least 3 hrs per week; or IV) intense physical activity more than 4 hours per week. The Physical Activity Scale will be used to assess average weekly physical activity of sleep, work, and leisure time [39].

### Medical history and status

Detailed information about the time of PCa diagnosis, disease stage, PSA level at the time of diagnosis, duration of ADT at baseline, previous radiation treatment or surgery and pre-existing comorbidities will be obtained from the participants’ medical records.

### Tracking and monitoring during soccer training

#### Heart rate

Participants will wear heart rate monitors (Polar Electro Oy, Kempele, Finland) to determine heart rate zones and intensity.

#### Activity profile

GPS monitors (GPSport, Melbourne, Australia) will be worn by participants in week 2 and 11 to record standing, walking and running times, as well as running speeds and distance covered.

#### Perceived exertion

In week 2 and 11 of the intervention participants’ perceived exertion and experience of flow will be determined with Visual Analogue Scales [40].

#### Adherence

Attendance and reasons for non-attendance of training sessions (e.g., muscle soreness, injury, in- or outpatient visits to the hospital) will be recorded in a training log book.

#### Adverse events

Serious adverse events occurring during the training will be reported immediately to the Unit for Patient Safety in the Capital Region of Denmark. Minor events related to physical contact or stumbling can occur during training, and only pain and soreness persisting for more than 24 h will be recorded.

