**Discussion:**

The FC Prostate trial will assess the safety and efficacy of a novel soccer-training approach to cancer rehabilitation on a number of clinically important health outcomes in men with advanced prostate cancer during ADT. The results may pave the way for innovative, community-based interventions in the approach to treating prostate cancer.

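### The only adverse-event rules described are tied to soccer training, so the trial cannot compare adverse events between arms although it says it will assess safety

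*Protocol article*

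**What the plan says.** The adverse-event text in the protocol article is two sentences, placed under the heading "Tracking and monitoring during soccer training".

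- **Serious events (reporting rule):** "Serious adverse events occurring during the training will be reported immediately to the Unit for Patient Safety in the Capital Region of Denmark".
- **Recording of minor events:** those from contact or stumbling in training are expected, and "only pain and soreness persisting for more than 24 h will be recorded".
- **Training log (Adherence):** "Attendance and reasons for non-attendance of training sessions" are entered, with soreness, injury and hospital visits given as examples of reasons.
- **Control arm (Study design; Control group):** a waiting list, offered soccer only after the study period. These men are encouraged to keep their baseline activity level, and no log is described for them.
- **Aim (Abstract, Discussion paragraph):** "The FC Prostate trial will assess the safety and efficacy of a novel soccer-training approach to cancer rehabilitation". The Background adds that safety information on exercise in men with bone metastases is scarce.
- **Both arms:** all assessments fall at baseline, 12 and 32 weeks. They include the EORTC QLQ-PR25 symptom questionnaire and DXA bone measures.

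**The concern.** A safety assessment in a randomised trial needs events collected alike in both arms. Here each described source of event data depends on taking part in soccer: the serious-event sentence, the minor-event sentence and the log. A control participant has no route into any of them.

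This matters because the population carries its own risk. The Background and Discussion attribute fractures, cardiovascular disorders and myocardial infarction to androgen deprivation, which both arms receive. Men with bone metastases are eligible unless the metastases cause activity-limiting pain. A fracture or cardiac event in a soccer participant could therefore come from the training, the treatment or the disease. The control rate is what would help tell these apart. Without it, a few events in the soccer arm cannot be put in context, and a report of few or no events says little about whether soccer adds risk. Events not collected prospectively and in the same way in both arms are hard to reconstruct later.

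**Working it through.** The plan gives no figure for safety, so the main check is a reading of the text. The arithmetic only sizes the window and the precision.

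**1. Who is covered under each reading of training.**
- *Training means the session.* Soccer arm: events in sessions, plus soreness beyond 24 h and logged absences. Control arm: nothing.
- *Training means the training period.* Soccer arm: serious events over the whole period, plus the same soreness and log data. Control arm: nothing.

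The two readings differ for the soccer arm only.

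**2. Data collected alike in both arms.** QLQ-PR25 measures symptoms and side-effects, and DXA measures bone mineral. Both can be compared at 12 and 32 weeks. Neither counts fractures, injurious falls, cardiovascular events or admissions.

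**3. Size of the window if the session is meant.** Inputs are from the Intervention group section.
- Weeks 1–4: 2 × 4 = 8 sessions of 15 + 2 × 15 = 45 min, giving 360 min.
- Weeks 5–8: 2 × 4 = 8 sessions of 15 + 3 × 15 = 60 min, giving 480 min (frequency taken as unchanged, since only the duration is said to rise).
- Weeks 9–12: 3 × 4 = 12 sessions of 60 min, giving 720 min.

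The 45 and 60 min agree with the session length in the abstract. The total is 28 sessions and 360 + 480 + 720 = 1,560 min = 26 h. Twelve weeks are 12 × 168 = 2,016 h, so the share is 26/2,016 = 1.3%.

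For 32 weeks (32 × 168 = 5,376 h), assume 60-min sessions in the last 20 weeks. With two sessions a week, the share is (26 + 40)/5,376 = 1.2%. With one session every second week, it is (26 + 10)/5,376 = 0.7%.

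**4. What equal recording could show with 40 men per arm.** The 40 comes from the lean-mass calculation, which reproduces. For 0.7 kg, SD 1.0 kg, two-sided 5% and 80% power, the t-test needs 33.02, rounded up to 34 per group. Then 34/0.85 = 40.
- Zero events in 40 men gives a one-sided 95% upper limit of 1 − 0.05^(1/40) = 7.2%. This holds for any fully observed arm of 40, so it measures precision, not the defect.
- Power to compare two event proportions (normal approximation, two-sided 5%; all rates are assumptions, as the article gives none): 32% for 5% vs 15%, 53% for 5% vs 20%, 71% for 5% vs 25%, 89% for 10% vs 40%.

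Only very large differences would be detected, so reporting should be descriptive.

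**The case against.** The strongest reply is that the serious-event sentence is a notification rule to an outside body. It does not say that other serious events go unrecorded, and the restrictive word belongs to the minor-event clause. The text also sits in a section about soccer sessions, and a journal article may leave general event procedures to the full protocol. This stands in part: one cannot say that the plan forbids recording control events. But the article is not merely silent. It gives training-bound rules alongside a stated safety aim, and the two do not fit.

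Second, safety is not among the listed purposes or the endpoints, and no between-arm event rate is promised. That is correct, and it lowers the severity. Lean mass, randomisation and the primary analysis are untouched.

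Third, a reader might infer that about 99% of events are missed, or that delayed fractures escape altogether. The documents do not support this. The 1.3% holds only if training means the session. It is a share of clock time, and soccer injuries would be expected to cluster in sessions. The 24 h soreness rule requires observation after the session, and the log would catch some delayed injuries as absences. A reader might also infer that there is no safety-related comparison at all, but QLQ-PR25 and DXA are measured in both arms.

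**Conclusion.** The point holds in limited form and should be fixed. Under either reading of training, no adverse-event recording is described for the control arm. The trial as described can give no between-arm comparison of adverse events, and this conflicts with the abstract's safety claim. For the soccer arm, the size of the gap depends on the wording: a window of about 1.3% of the time over 12 weeks if sessions are meant, and far wider if the training period is meant. How many events would go unrecorded cannot be derived from the documents. The conclusion rests on the article alone. If the full protocol already provides for event recording in both arms, the article's text needs only to say so.

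**What to change.** From randomisation to week 32, record in both arms and regardless of setting: serious adverse events, fractures, injurious falls, cardiovascular events and hospital admissions. Use the same structured questions at the existing 12- and 32-week visits. Report them descriptively by arm with exact confidence intervals. Keep session-related soreness and injuries as a separate soccer-only table, so that closer observation of that arm does not distort the comparison. State whether the serious-event sentence refers to sessions or to the training period.

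If recording is not widened, limit the safety statement in the abstract to training-related events.

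The cost is a short form at two visits that already take place, a short amendment and some added data entry. Confirming events from hospital records would be an extra step, because the Medical history and status section describes only history and baseline information. The change concerns data collection and reporting only.

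No increase in sample size is implied: with 40 men per arm the comparison remains descriptive.

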### Statistical considerations

#### Sample size calculations

Since recreational soccer has not previously been applied as a rehabilitation strategy for men with PCa, the possible effect size on LBM is unknown. However, Krustrup et al. [41] have shown that the effect of soccer training on LBM is comparable to that of progressive resistance exercise [42]. In men with PCa undergoing ADT progressive resistance exercise has yielded increases in LBM of 0.7 kg after 12 weeks of training [15]. To detect a 0.7 kg difference in LBM between the groups, assuming a standard deviation (SD) of 1.0 kg, 34 patients are needed in each group with a significance level (two-sided) of 5% and a power of 80%. Due to possible dropouts we plan to include 40 patients in each group.

#### Data analyses

Data entry will be undertaken using a secure web server and statistical analysis will be performed using Statistical Analysis Systems (SAS) version 9.2. The statistician will prepare results with no knowledge of the randomization coding. The primary endpoint will be reported as a two-sample t-test comparing change scores in the two randomization groups. Significance level will be set at 0.05.

Regarding secondary outcomes, the continuous variables, i.e., VO_2_max, HRmax, waist and hip circumferences, CMJ, and stair climbing parametres, and the patient reported outcomes, respectively, will be reported as either means with corresponding 95% confidence limits or as medians and interquartile range (IQR). For count data, i.e., the Flamingo balance test and the sit-to-stand test, Poisson regression will be used, and categorical data, i.e., single questionnaire items, will be reported as proportions and compared across randomization groups using chi-squared tests or logistic regression.

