Therefore the purpose of the present study is to investigate 1) the effects of 12 weeks of recreational soccer on body composition, fitness, cardiac structure and function, peripheral vascular function, blood pressure, physical function parameters, postural balance, muscle strength, glucose tolerance, insulin sensitivity, and markers of inflammation and bone metabolism and 2) whether potential physiological and patient-reported effects of the 12 week soccer training intervention can be maintained or improved further with an additional 20 weeks training at a reduced training volume. The primary study endpoint is changes in LBM from baseline to 12 weeks.

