### Randomization

After successful completion of all baseline assessments participants are randomized 1:1 to the soccer intervention or control group. The randomization process will be conducted by a research consultant at The Copenhagen Trial Unit who has no other involvement in the study. The study flowchart is presented in Figure 1.

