### Study assessments

All assessments will take place at baseline, and after 12 weeks and 32 weeks. Measurement of body composition, peripheral vascular function, glucose tolerance, blood pressure, and blood markers will be performed in the morning after an overnight fast. Subjects will be instructed to avoid intake of medication, caffeine and vitamins, and to abstain from tobacco use for 12 h prior to the above mentioned tests and to avoid strenuous physical activities 48 h prior to all examinations.

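### The primary t-test of 12-week change scores can use only men with both scans and adjusts for baseline lean mass only by subtraction; a longitudinal model would need a weaker missing-data assumption at almost no cost

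*Protocol article*

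**What the plan says.** The end of the Background section defines the endpoint: "The primary study endpoint is changes in LBM from baseline to 12 weeks". Data analyses then names the test: "The primary endpoint will be reported as a two-sample t-test comparing change scores in the two randomization groups". No covariate is given.

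Sample size calculations sets out the target ("To detect a 0.7 kg difference in LBM between the groups, assuming a standard deviation (SD) of 1.0 kg") and the result ("34 patients are needed in each group with a significance level (two-sided) of 5% and a power of 80"%). It adds: "Due to possible dropouts we plan to include 40 patients in each group". No dropout rate is stated.

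The design collects more LBM data than the test uses. Under Randomization, "After successful completion of all baseline assessments participants are randomized 1:1", so every randomised man should have a baseline scan. Under Study assessments, "All assessments will take place at baseline, and after 12 weeks and 32 weeks", so a second follow-up scan is planned for everyone.

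The article does not define the analysis set or a missing-data method.

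**The concern.** A change score exists only when both scans exist. A two-sample t-test on it therefore leaves out any man without a 12-week scan, unless a value is imputed, and no imputation is mentioned. His 32-week scan, if he has one, is not used. The result is then unbiased only if the men without a week-12 scan would have changed, within each arm, like those who have one.

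That is a strong assumption in this trial. Patients cannot be blinded, controls are waiting for the intervention, and the article itself expects that soreness, injury and hospital visits may keep men from training. Losses could differ between arms and be related to outcome.

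The change score also fixes the coefficient of baseline LBM at 1. If the true slope is lower, for example because of scan error, a chance imbalance in baseline LBM carries partly into the estimate. The size of this has to be worked out, because LBM at two visits is very highly correlated.

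**Working it through.** **Inputs from the article.** Difference 0.7 kg; SD 1.0 kg (read as the SD of change, because the test is on change scores); two-sided 5%; power 80%; 1:1 allocation; 34 needed and 40 enrolled per arm.

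**Assumed, because the article gives no figure.** Baseline SD of LBM, s, from 3 to 8 kg; equal variance at both visits.

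**1. The plan's own figure.** The exact two-sample t calculation for 0.7/1.0 gives 33.02, so 34 per arm, as stated. Power is 81.2% at 34 and 87.1% at 40. The implied dropout allowance is 1 − 34/40 = 15%, that is 6 per arm or 12 of 80.

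**2. Precision effect of baseline adjustment.**
- Correlation between visits: ρ = 1 − 1.0²/(2s²), which is 0.944 (s = 3), 0.980 (s = 5) and 0.992 (s = 8).
- Variance of the adjusted relative to the change-score estimate, slope known: (1 + ρ)/2, which is 0.972, 0.990 and 0.996.
- The slope must be estimated. At n = 34 per arm this multiplies the variance by about 1 + 1/(2n − 4) = 1 + 1/64 = 1.0156.
- Expected ratio: 0.972 × 1.0156 = 0.987; 0.990 × 1.0156 = 1.005; 0.996 × 1.0156 = 1.012.

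The break-even is (1 + ρ)/2 = 64/65, or ρ = 0.969. Above that, adjustment is marginally less precise. A real gain needs change itself to be related to baseline. With a correlation of 0.3 between change and baseline, for example, the ratio is (1 − 0.09) × 1.0156 = 0.924.

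**3. Effect of a chance imbalance.** A 2-SD imbalance is 2s√(2/34): 1.46 kg for s = 3 and 3.88 kg for s = 8. The change-score estimate moves by (1 − ρ) times this, which simplifies to √(2/34)/s = 0.243/s: 0.08 kg for s = 3, 0.05 kg for s = 5, 0.03 kg for s = 8. That is 4% to 12% of 0.7 kg. The standard error of the difference is 1.0 × √(2/34) = 0.24 kg.

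**4. What missing scans could do.** Illustration: 15% of the soccer arm is lost, their change would have differed from completers' by 0.5 to 1.0 kg, and there is no such difference among controls. The complete-pair estimate shifts by 0.15 × 0.5 = 0.075 kg to 0.15 × 1.0 = 0.15 kg, which is 11% to 21% of 0.7 kg.

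**5. What the longitudinal model recovers.** A simulation assumed a correlation of 0.6 between the 12- and 32-week changes, all men scanned at week 32, and loss at week 12 in the soccer arm that depends on week-32 LBM. With a true difference of 0.70 kg, the t-test averaged 0.76 kg and the model 0.69 kg, with no loss of precision. The scenario is built so that data are missing at random given observed LBM, which is the case the model handles. It does not show that all of the shift in step 4 would be removed.

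**The case against.** The strongest reply is that nothing is miscalculated or contradictory. The test matches the endpoint and the sample size, and under randomisation with complete data it is valid and unbiased. This stands. A reader might infer that the test ignores baseline LBM or gives a biased answer by design. It does neither: it subtracts baseline, and what is missing is adjustment beyond that.

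Second, adjustment is often recommended for power, and a reader might expect a gain here. Step 2 shows about none for LBM unless change is related to baseline. The imbalance effect in step 3 is also small against a standard error of 0.24 kg.

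Third, a reader might infer that the article excludes men without a 12-week scan, or that 15% of men will be discarded. No section says so. The move from 34 to 40 is an ordinary dropout allowance, and the analysis set and missing-data handling may be covered in a full protocol or analysis plan not shown here. That silence is not the point. The point is the named test, which by its construction needs both scans.

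Fourth, the model does not rescue everyone. With baseline as a covariate, a man with neither follow-up scan contributes no outcome. The number who would miss week 12 but return at week 32 is unknown, so the benefit cannot be sized from the article. This also stands.

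Nor can larger gains be claimed for the secondary outcomes, because Data analyses does not fix change-score t-tests for them.

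**Conclusion.** The point holds as an improvement to a stated method that the plan should adopt; it is not an error that invalidates the trial. The named test uses only complete pairs where about 15% dropout is implied, and it leaves the 32-week scan unused for the primary question.

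The benefit lies in the missing-data assumption: missing at random given observed LBM, in place of completers standing for everyone in their arm. In the assumed scenario this removed an error of about 0.06 kg (0.76 against 0.70 kg). The real size depends on how many men miss only week 12, and why. Bias from data missing not at random would remain.

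The precision effect for LBM is about nil (variance ratio 0.99 to 1.01), and a 2-SD imbalance moves the change-score estimate by about 0.03 to 0.08 kg. Both figures rest on the planned change SD of 1.0 kg, an assumed baseline SD of 3 to 8 kg and equal visit variances.

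**What to change.** Make the primary estimate the 12-week group difference in LBM, with 95% CI, from a longitudinal model of the 12- and 32-week values of all randomised men as allocated. Include group, visit, group-by-visit, and baseline LBM by visit. A version that treats baseline as a further outcome with equal group means also takes in men who have only a baseline scan. Keep the change-score t-test as a sensitivity analysis. State the missing-at-random assumption and add a sensitivity analysis for departures from it. Settle this before unblinding, so that the choice cannot depend on observed imbalance or dropout.

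The cost is plan wording and one mixed-model call in the SAS software already named, about one degree of freedom, and reliance on a model. No new data, no additional patients and no change to the sample size are needed.

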#### Secondary study endpoints

Secondary outcomes include body composition, measures of physical functioning, assessment of cardiovascular and metabolic function, blood test values and patient-reported outcomes.

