#### Flamingo balance test

Postural balance will be assessed with a modified single-leg flamingo balance test [22]. Subjects are instructed to stand on one foot on a 3 cm wide and 5 cm high metal bar with their eyes open for one min. Subjects are permitted to move their arms and non-standing leg to assist balancing. The number of falls will be counted and used as a measure of postural balance.

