#### Sit-to-stand test

Using a chair fixed to the ground with a seat 45 cm above the ground subjects will be instructed to sit in the middle of the chair, back straight, arms crossed over their chest, feet flat on the floor. A mechanical contact in the seat is connected to a computer which automatically counts the number of rises. Correct standing technique will be demonstrated first slowly, then quickly. Subjects will be allowed to practice for two-three repetitions before the start of the test. On the signal “go” the subject will be asked to stand, then return to the seated position, as many times as possible in 30 s [26].

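### Poisson regression is named for the Flamingo and sit-to-stand counts with no dispersion allowance, so their standard errors may be too small or too large

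*Protocol article*

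**What the plan says.** The Data analyses section of the protocol article gives one inferential method for the two tests: "For count data, i.e., the Flamingo balance test and the sit-to-stand test, Poisson regression will be used". It mentions no scale parameter, robust variance or other count model, and it lists no model terms. On testing it adds "Significance level will be set at 0.05"; the two-sided 5% level appears under Sample size calculations.

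The outcomes are defined under their own headings. In the Sit-to-stand test the man rises from a chair "as many times as possible in 30 s". In the Flamingo balance test he stands on one foot on a narrow bar "with their eyes open for one min", and "The number of falls will be counted and used as a measure of postural balance". Both are physical function tests and therefore secondary: "Secondary outcomes include body composition, measures of physical functioning". All assessments take place at baseline, 12 weeks and 32 weeks, so a baseline count will exist for each man. No mean, SD or distribution is given for either test.

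**The concern.** Poisson regression in its ordinary form does not estimate the variance; it sets it equal to the mean. That suits counts of independent random events at a common rate. Neither test is clearly of that kind.

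- **Sit-to-stand.** The number of rises is a capacity score paced by the man himself. It is an integer, but nothing ties its spread to the square root of its mean. The same section treats other performance tests, such as jump height and stair climbing, as continuous.
- **Flamingo.** Falls in one minute depend on balance ability, which differs between men. Any such difference in the underlying rate adds to the Poisson variance, so over-dispersion is to be expected.

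If the variance exceeds the mean, intervals are too narrow and false-positive group differences become too frequent. If it falls below the mean, intervals are too wide and real differences are missed. Postural balance and physical function are both named in the study's purpose, so a spurious or a missed effect would be reported as a finding of the trial.

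**Working it through.** **Inputs from the article.** Poisson regression for both counts; significance level 0.05, two-sided; 1:1 allocation; 34 evaluable men per group. The article gives no figure of its own for these two tests. Its only sample size is for lean body mass ("To detect a 0.7 kg difference in LBM between the groups, assuming a standard deviation (SD) of 1.0 kg"), and it reproduces. The normal approximation, 2 × (1.96 + 0.84)² × (1.0/0.7)² = 32.0, rounds up to 33 per group; the t-based solution is 33.02, rounded up to 34, with 81.2% power at 34. With 15% dropout, 34/0.85 = 40. That result has no bearing on the present point beyond supplying 34 per group.

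**Formulas.** Let φ = variance/mean.
- Model standard error divided by true standard error = 1/√φ.
- Actual two-sided type I error of the Wald test = 2 × [1 − Φ(1.96/√φ)].
- Power for an effect that has 80% power under correct errors = 1 − Φ(1.96/√φ − 2.80).

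**Results over an assumed range of φ.**

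| φ (assumed) | Model SE / true SE | Actual type I error |
|---|---|---|
| 0.5 | 1.41 | 0.6% |
| 0.75 | 1.15 | 2.4% |
| 1 | 1.00 | 5.0% |
| 1.5 | 0.82 | 11% |
| 2 | 0.71 | 17% |
| 3 | 0.58 | 26% |

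For example, at φ = 3, 1.96/√3 = 1.13 and 2 × [1 − Φ(1.13)] = 26%. At φ = 0.5, 1.96/√0.5 = 2.77, giving 0.6%; power there is 1 − Φ(2.77 − 2.80) = 51% instead of 80%.

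**Sit-to-stand, unadjusted** (34 per group, 20,000 simulated trials, no true effect; means and SDs assumed). The direction turns on whether the SD lies below or above √mean.
- Mean 18 (√18 = 4.24): type I error 0.5% at SD 3, 3.9% at SD 4, 9.7% at SD 5, 16.6% at SD 6.
- Mean 22 (√22 = 4.69): 2.2% at SD 4, 6.7% at SD 5, 12.1% at SD 6.

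**Sit-to-stand, adjusted for baseline.** Adjustment removes explained variance. With mean 18 and SD 5, φ = 25/18 = 1.39; with an assumed baseline correlation of 0.7, the residual φ is about 1.39 × (1 − 0.49) = 0.71. In simulation (34 per group, 1,500 trials, so a Monte Carlo error of about √(0.05 × 0.95/1,500) = 0.6 percentage points):

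| Mean, SD, correlation (assumed) | Adjusted Poisson | Adjusted, robust errors |
|---|---|---|
| 18, 5, 0.7 | 1.7% | 5.8% |
| 18, 6, 0.8 | 1.9% | 6.3% |
| 22, 5, 0.7 | 0.9% | 5.6% |

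So in these scenarios the same outcome is anti-conservative without baseline and conservative with it; robust errors bring the rate close to 5%.

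**Flamingo** (negative binomial counts, 34 per group, 20,000 simulated trials; means and SDs assumed): type I error 12.8% at mean 15, SD 5; 21.8% at mean 10, SD 5; 27.0% at mean 5, SD 4.

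**The case against.** The strongest objection is that a journal article condenses the plan. The variance estimator, dispersion handling and covariates for two secondary outcomes are details that commonly go into the analysis plan, which is not shown. A Poisson model with a Pearson scale or sandwich variance is still Poisson regression, so the remedy is compatible with the sentence as printed. This stands in part: the article does not prove that an unscaled model will be run. It did not, however, leave the model family open. It names Poisson regression as the only method for both outcomes and classes a maximal-effort score as count data. That is a stated choice that fits poorly.

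A second objection is that the size rests wholly on assumed dispersion. That is correct. Near φ = 1 the harm is small: at mean 18 and SD 4 the type I error is 3.9%.

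A reader might infer more: that the errors will go in opposite directions, too small for Flamingo and too large for sit-to-stand. The documents do not support this. They give no dispersion, and the argument for under-dispersed sit-to-stand scores depends largely on baseline adjustment, which the article does not mention. Without it, both tests could err the same way. Nor can one conclude that baseline is left out: the section lists no model terms, and silence does not exclude a covariate.

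**Conclusion.** The point holds as a concern about a stated method that is correct only under an assumption the outcome definitions do not support. Over an assumed φ of 0.5 to 3, the actual type I error at a nominal 5% lies between 0.6% and 26%. For Flamingo, standard errors that are too small are the more likely outcome, on the reasonable but undocumented assumption that men differ in balance. For sit-to-stand the direction is open. All means, SDs, correlations and values of φ used here are assumptions. Only secondary outcomes are affected; the primary t-test on change in lean body mass does not depend on this choice. It is worth correcting because the remedy does not require knowing the direction of the departure.

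**What to change.** Replace the sentence on count data by one of two specifications:

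1. A log-link count model for both tests, with robust (sandwich) or Pearson-scaled standard errors and the baseline count as covariate.
2. Linear ANCOVA on the baseline score for sit-to-stand, and negative binomial or quasi-Poisson regression with baseline for Flamingo falls.

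In either case report the adjusted ratio or difference with its 95% confidence interval. The second option changes the sit-to-stand effect from a ratio to a difference in repetitions.

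The cost is one sentence in the plan and one or two lines of code in the SAS software already named. No new data are needed, since baseline is already measured. The downsides are a little more analysis work and, if the counts are over-dispersed, wider intervals. With about 34 men per group, sandwich errors may also be slightly liberal (5.6% to 6.3% in the simulations above).
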